For participants in both control and treatment groups, outcomes will be measured at baseline, 1 year and 5 years after surgery. The primary outcome is GORD symptom scores (assessed with the GERD-HRQL survey). Secondary outcome(s) are GORD symptom scores (assessed with the GERD-HRQL survey) at 5 years, the percentage of total time spent with pH < 4 in the oesophagus, the presence and severity of oesophagitis, and patient-reported outcomes. Gastrointestinal-specific quality of life will be assessed using the SAGIS questionnaire^42^ (including dysphagia, belching, bloating, flatulence, and altered bowel habit), while overall quality of life will be assessed using SF-6Dv2^43,44^. The operative metrics and surgical morbidity measures will be operating time (measured in minutes), pain score (measured using a visual analogue score and oral morphine equivalents), length of hospital stay (measured in days), the Comprehensive Complication Index^61^, the development of complicated gallstone disease, and readmission rate (at 90 days). Bodyweight changes will be monitored. With respect to the changes in pathophysiological parameters contributing to GORD, the transient lower oesophageal sphincter relaxation episodes and duration on high-resolution manometry and bladder pressure measurement (as a surrogate for intra-abdominal pressure) will be measured both before and after surgery.

For randomization, an adaptive procedure will be used to stratify patients according to sex, BMI (class I or uncomplicated class II), and percentage of time with oesophageal pH < 4 (4–10 per cent and more than 10 per cent), with the use of a ‘biased coin’ procedure to balance treatment assignments^60^. The symmetric Kullback–Leibler divergence minimization method, which allows the use of both continuous and categorical factors will be used^62^. A 1:1 assignment will be used with a block size of six. The goal is that the patient will be kept blinded until after the operation. To achieve this, group allocation will be performed by a database manager (non-clinician) the morning before surgery (to facilitate operating room scheduling and equipment preparation). It will be directly communicated to the operating surgeon.

For blinding, the allocation sequence will be concealed from researchers responsible for assigning participants. The patient will be kept blinded until after the operation. Where possible, data analysis will be conducted in a blinded fashion.

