### Ethical considerations

The research project will be conducted in full conformance with principles of the Declaration of Helsinki, Good Clinical Practice and within the laws and regulations of Queensland and Australia. All Metro South Health Research requirements will be complied with at all times.

All participating surgeons are Australian-trained and Fellows of the Royal Australasian College of Surgeons. All have had post-vocational fellowship placements in the sub-specialty of upper gastrointestinal surgery. All have public hospital appointments as consultant surgeons and have had sufficient training to be granted credentialling in both operation types. All participating physicians are Fellows of the Royal Australasian College of Physicians and are recognized sub-specialists in the field of gastroenterology. All listed investigators have been consulted about the trial and, having had the opportunity to review and optimize the trial protocol, have reached a consensus.

As would occur in standard clinical practice, the recruiting surgeon will be responsible for the provision of sufficient information for the patient to make an informed decision about undergoing an operation. Initially, the surgeon will counsel the patient on what the usual clinical pathway and operation would be (LF) if they decline trial participation, including the benefits of LF as well as general and material risks. The surgeon will also outline the uncertainty about whether the current standard of care (LF) is the best operation in their circumstances. The surgeon will then outline the requirements for trial participation and discuss the alternative operation (LRYGB), including the benefits and risks in sufficient depth for the patient to make an informed decision about participation. Information will be given verbally and in written form. If English proficiency is insufficient, a credentialled translator will be provided, in keeping with usual clinical standards for informed consent. Generally, this process would happen in the outpatient clinic, the patient would return home for an interval of approximately 6 weeks, then return to a second appointment for further discussion and counselling, at which time a decision may be reached. If participation is declined, the patient will revert to the current standard clinical pathway. Consent can be withdrawn at any time, although for obvious reasons this should generally be withdrawn before surgery.

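### Randomisation is specified both as biased-coin minimisation and as fixed blocks of six with nothing linking them; if the block is used, its published length weakens concealment

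*Protocol article*

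**What the plan says.** The randomisation paragraph in the Outcomes section of the protocol article makes three statements in a row.

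- Patients are stratified adaptively by sex, BMI class and percentage of time with oesophageal pH below 4, "with the use of a ‘biased coin’ procedure to balance treatment assignments". No coin probability is given.
- "The symmetric Kullback–Leibler divergence minimization method, which allows the use of both continuous and categorical factors will be used".
- "A 1:1 assignment will be used with a block size of six".

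The article does not say whether the block is a start-up phase, or whether it runs overall, within strata or within hospital.

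On who knows what: "group allocation will be performed by a database manager (non-clinician) the morning before surgery", and of the result, "It will be directly communicated to the operating surgeon". The article also states that "the allocation sequence will be concealed from researchers responsible for assigning participants". Under Ethical considerations, "the recruiting surgeon will be responsible for the provision of sufficient information for the patient to make an informed decision". The Data management and monitoring section describes the participating surgeons, as a group, as assessing, counselling and operating. Under Statistical considerations, a pilot of 20 patients (10 per arm) is run at one hospital, after which three more hospitals join.

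**The concern.** Minimisation with a biased coin sets each assignment from the current imbalance plus a random element. A permuted block sets it from the slots left in the block. A programmer given this text could build two different systems, and a reader of the final report could not tell which one was used.

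The second issue is concealment. If blocks are used, one fixed length has been published, and the people told the allocations belong to the same group that recruits. Someone who can work out the next assignment can influence who receives it. The primary outcome is a patient-reported symptom score and patients are blinded only until after the operation, so a selection effect would be hard to detect or correct later.

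**Working it through.** The article states no predictability figure to reproduce. The inputs from the article are the 1:1 ratio, the block of six and the pilot of 20. The coin probability p is not stated, so values from 0.6 to 0.9 are assumed.

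**1. Block of six, all earlier assignments in the block seen.** There are C(6,3) = 20 possible blocks. With a and b patients already assigned to the two arms, the best guess is right with probability max(3−a, 3−b)/(6−a−b), and the next assignment is certain when a = 3 or b = 3.

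| Position | Certain | Best guess right |
|---|---|---|
| 1 | 0 | 0.50 |
| 2 | 0 | 3/5 = 0.60 |
| 3 | 0 | 0.4×3/4 + 0.6×1/2 = 0.60 |
| 4 | 2/20 = 0.10 | 0.1×1 + 0.9×2/3 = 0.70 |
| 5 | 8/20 = 0.40 | 0.4×1 + 0.6×1/2 = 0.70 |
| 6 | 1.00 | 1.00 |
| Sum | 1.5 | 4.1 |

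Certain: 1.5/6 = 25%. Guessed correctly: 4.1/6 = 68.3%.

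**2. Only part of the block seen.** Suppose each earlier assignment is seen independently with probability f, and the observer knows where the block starts. An assignment is certain only if all three earlier patients of one arm were seen, so the certain share is 25% × f³.

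- f = 1/2: 25% × 1/8 = 3.1% certain. Simulation of 200,000 blocks gives 58.4% guessed correctly.
- f = 1/4: 25% × 1/64 = 0.4% certain, and 54.8% guessed correctly by simulation.

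**3. Biased coin alone.** As a simple stand-in for the minimisation, take a coin acting on the overall arm difference, with q = 1 − p. Counting the paths that return to balance gives P(3:3 after six) = p³(1 + 2q + 2q²). In the long run the arms are level before a share π = (1 − q/p)/2 of assignments, so the best guess is right with probability p − (p − 1/2)π. No assignment is certain while p < 1.

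| p | 3:3 after six | Best guess right |
|---|---|---|
| 0.6 | 46% | 58.3% |
| 2/3 | 56% | 62.5% |
| 0.7 | 61% | 64.3% |
| 0.8 | 76% | 68.8% |
| 0.9 | 89% | 72.2% |

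A simulation of 180 patients agrees with the last column to within 0.2 percentage points. A block of six gives 3:3 after six patients in 100% of runs. The two rules are therefore different allocation laws.

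**4. Pilot balance.** 20 = 3×6 + 2. Under one running block, 10:10 requires the last two patients to be split: 2 × 3/6 × 3/5 = 60%.

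**The case against.** This is a condensed article. A hybrid design, such as blocks for a start-up phase followed by minimisation, is possible, and the full protocol may describe one. That stands: the defect is an unreconciled description, and it would be too strong to say that the two methods can never be combined. But the article states both rules for the same trial with nothing to separate them, which is different from leaving a detail out.

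The concealment risk can also be overread.

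- A reader might infer that surgeons see every assignment. The article says only that each allocation goes to the operating surgeon. It does not say that anyone sees them all across four hospitals, or that the recruiting and operating surgeon are the same person for a given patient.
- A reader might infer that surgeons control scheduling. The article mentions scheduling only as a reason for the timing of allocation.
- A non-clinician allocates after consent, on the morning before surgery, so slots are filled in order of surgery rather than of recruitment. This makes steering at enrolment difficult. It does not prevent a late withdrawal, or a change of list order among patients who have already consented.
- If blocks ran within the 2×2×2 = 8 factor cells, an observer would have to track each cell separately.

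Finally, setting 68% against 50% would flatter the remedy. The 50% belongs to simple randomisation, and a simple coin at 0.8 is about as guessable as the block (69%).

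**Conclusion.** The point holds in limited form. The randomisation cannot be carried out or reported as written, because a fixed block and a biased coin cannot both decide the same assignment.

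The effect on concealment is conditional. The 25% certain and 68% guessable are upper figures for one running block followed in full from its start. That is most plausible in the single-hospital pilot, which spans just over three blocks (20/6 = 3.3). At half visibility the figures fall to about 3% and 58%. They apply only if blocks are actually used.

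Two further inferences are not supported. The ambiguity does not leave an adjusted analysis without its factors: the Outcomes section names all three, and the Statistical considerations section states no adjusted analysis. Nor does the block secure 10 per arm in the pilot, since one running block gives that split only 60% of the time.

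The biased-coin figures rest on assumed probabilities and a single-factor coin. Minimisation over three factors may be harder to follow.

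**What to change.** Delete the block clause and describe one method: 1:1 allocation by Kullback–Leibler minimisation over the three named factors, with a random element below 1. Removing the block takes the share of certain assignments from as much as 25% to zero. If guessability is to fall as well, choose a probability nearer 0.67 (about 62%) than 0.8 (about 69%). Record the probability in a restricted document, and keep it and the running imbalance from the surgeons. Allocation by the database manager can stay as it is.

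If a hybrid is intended, say where the block applies and use varying, undisclosed block sizes.

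Adding hospital as a minimisation factor is an optional, low-cost addition, given four hospitals and surgical technique left partly to the operating surgeon. It is separate from the contradiction.

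The cost is a wording change and a small change to the allocation program. Exact 3:3 balance in every six patients is lost. The lower probability also balances less tightly: 3:3 after six patients in 56% of runs at 2/3, against 76% at 0.8 for the simple coin.

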### Statistical considerations

There are limited data to guide the sample size calculation. A pilot phase of 20 patients (10 in each arm)^63^ will be completed at the Upper Gastrointestinal Surgery Unit, Princess Alexandra Hospital. This will allow an assessment of recruitment rate and an analysis of the primary outcome to enable the power calculations and trial duration to be recalculated and ensure that the trial remains practical and can be completed. In addition, any initial logistical issues can be resolved. Thereafter, the trial will be extended across Logan Hospital, QEII Jubilee Hospital and the Royal Brisbane and Women’s Hospital.

The trial will be powered based on the primary outcome alone. Using *α* = 0.05, *β* = 0.8, a randomization ratio of 1: 1 and a mean(s.d.) GERD-HRQL score of 8(8) after LF in class I and II obesity^64^ and 5 after LRYGB^65^, a sample size of 164 would be required. Assuming a 10 per cent dropout, there would need to be 91 patients in each arm. This equates to approximately 2 years of referrals of eligible patients to the Princess Alexandra Hospital alone. Assuming participation of the other hospitals and 50 per cent uptake, a conservative estimate is that recruitment will take approximately 3 years.

Acknowledging the lack of data to guide power calculations and hence the possibility that the alternative treatment (LRYGB) may give the same mean GERD-HRQL score as the control treatment (LF), a planned non-inferiority analysis will also be performed. Using *α* = 0.05, *β* = 0.9, a randomization ratio of 1: 1, a mean(s.d.) GERD-HRQL score of 8(8) after LF in class I and II obesity and a non-inferiority limit (d) of 4, a sample size of 138 is required. Assuming a 10 per cent dropout, there would need to be 77 patients in each arm.

Given that both superiority and non-inferiority analyses are planned, it is appropriate to perform both intention-to-treat and per-protocol analyses. Continuous data will be tested using a Student’s *t* test if data are normally distributed or otherwise a Mann–Whitney *U* test. Normality of continuous data will be assessed with the Shapiro–Wilks test. Categorical data will generally be assessed using the chi-squared test or Fisher’s exact test when the assumptions of the chi-squared test are not met. All *P* values will be two-tailed (except for non-inferiority analysis), and significance will be set at 0.050.

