### Operative complications

All patients having a postoperative complication (defined by the Clavien–Dindo and Comprehensive Complication Index) will have their complication recorded and case reviewed. A planned interim analysis at the conclusion of the pilot phase (after 10 cases) will be conducted. The research team will maintain full compliance with the Metro South Hospital and Health Service Research Management Monitoring Procedure, including self-assessment, external review, and annual reports.

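### The sample size may be reset from the primary outcome in 20 pilot patients without being limited to the blinded pooled s.d., and the end of the pilot is put at both 20 patients and 10 cases

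*Protocol article*

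**What the plan says.** The Statistical considerations section of the Protocol article announces "A pilot phase of 20 patients (10 in each arm" at one hospital. One stated purpose is an "analysis of the primary outcome to enable the power calculations and trial duration to be recalculated". The same trial then continues: "Thereafter, the trial will be extended across Logan Hospital, QEII Jubilee Hospital" and a further hospital follow.

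The size to be revised rests on "a randomization ratio of 1: 1 and a mean(s.d.) GERD-HRQL score of 8(8) after LF in class I and II obesity", an LRYGB mean of 5, α of 0.05 and 80% power (printed as β = 0.8). From these the article concludes that "a sample size of 164 would be required", or 91 per arm after 10% dropout. On the final tests it says that P "values will be two-tailed (except for non-inferiority analysis), and significance will be set at 0.050".

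On blinding, the Outcomes section says in general terms: "Where possible, data analysis will be conducted in a blinded fashion". The Operative complications section adds: "A planned interim analysis at the conclusion of the pilot phase (after 10 cases) will be conducted".

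The article does not say whether the pilot analysis compares the arms or pools them, or whether pilot patients enter the final test.

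**The concern.** An unrestricted analysis of the primary outcome that feeds a new power calculation can take two quite different forms. One uses only the blinded variance, which is a standard and nearly harmless step. The other puts the observed difference between arms into the formula. The wording permits both. The section also names doubt about the effect itself, since it allows that the two operations may give the same mean score, so the second form is a natural one to fall into.

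Under the second form, N would follow a quantity that 20 patients cannot estimate. The trial would tend to be small when the pilot happens to look favourable, and the unadjusted final test could exceed its nominal 5%.

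The count is a separate difficulty. Two sections describe the end of the same pilot phase, one at 20 patients and the other after 10 cases.

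**Working it through.** **Inputs** (Statistical considerations): LF mean 8, s.d. 8; LRYGB mean 5, so a difference of 3; two-sided α 0.05; power 80%; pilot of 10 per arm. Assumptions: s.d. 8 in both arms, normal scores, no pilot dropout, and the mean GERD-HRQL score as the outcome, as in the article's own sample size calculation.

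**1. The plan's own figure.** n per arm = 2(1.960 + 0.842)² × 8² / 3² = 1004.7 / 9 = 111.6, so 112 per arm (224 in total). The stated 164 (82 per arm) is not reproduced. With 82 per arm the standard error is 8√(2/82) = 1.249, and power is Φ(3/1.249 − 1.960) = Φ(0.44), about 67%. A total of 164 would need a common s.d. of about 6.9, or an LRYGB s.d. of about 5.5; neither is given. The non-inferiority figure is reproduced: 2(1.645 + 1.282)² × 64 / 16 = 68.5, so 69 per arm and 138 in total.

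**2. What 10 per arm can show about the difference.** SE = 8√(2/10) = 3.58. The 95% half-width is 2.101 × 3.58 = 7.5 points. If the true difference is 3, the observed one is zero or reversed with probability Φ(−3/3.58) = 20%.

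**3. N if the observed difference sets it.** With s.d. 8, n per arm = 1004.7/d². This is below 82 when |d| > √(1004.7/82) = 3.50. With a true difference of 3:
- P(d > 3.50) = 1 − Φ(0.50/3.58) = 0.444
- P(d < −3.50) = Φ(−6.50/3.58) = 0.035
- Total: about 48%

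When the s.d. is estimated as well, simulation (400,000 trials per setting) gives a median n per arm of 87, an interquartile range of 31 to 378, and only 11% of trials within 25% of 112.

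**4. N if only the s.d. is used, with the difference fixed at 3.** The s.d. estimated on 18 degrees of freedom has a central 95% range of 5.41 to 10.59, which gives n of 52 to 196 per arm. The blinded pooled s.d. gives 55 to 201, with median 112. This is imprecise but centred correctly.

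**5. Type I error of an unadjusted final t test at two-sided 0.05** (simulation, look at 10 per arm):

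| Rule for N | Pilot patients kept | Pilot patients excluded |
|---|---|---|
| Observed difference and s.d., N free to fall | 0.084–0.085 | 0.050 |
| Same rule, N not below 82 per arm | 0.054–0.055 | 0.050 |
| Within-arm s.d. only, difference fixed at 3 | 0.051 | 0.050 |
| Blinded pooled s.d., difference fixed at 3 | 0.050 | 0.050 |

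For an effect-driven N with floors of 11 to 40 and caps of 182 to 300 per arm, a separate simulation (20,000 null trials per setting) gave 0.060 to 0.082.

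**6. The two counts.** Statistical considerations has 10 in each arm and 20 in all. Operative complications has the same phase concluding after 10 cases. As written, the two do not agree.

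**The case against.** The strongest reply is that the article never says the look compares the arms. It notes that data for the sample size are limited, so estimating the s.d. fits the text, and it promises blinded analysis where possible. Inflation needs three things together: N driven by the observed difference, pilot patients kept, and no adjustment. None is stated. The detailed rule may also stand in a fuller protocol or analysis plan that is not shown. All of this stands, and a reader who infers that the pilot look will inflate the type I error goes further than the text allows.

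Other tempting inferences fail for similar reasons:
- **An efficacy look at only 5 per arm.** The 10-case analysis sits under operative complications. It may concern safety only, or it may mean 10 per arm.
- **Other hospitals waiting for 1-year outcomes.** They follow the pilot phase, but no section ties their opening to 1-year data or stops recruitment at the first hospital meanwhile. A delay cannot be derived.
- **Investigators seeing the arm difference early.** The article does not say who would see pilot results, and it provides for an independent monitoring board with a statistician.
- **Lower power than planned.** In simulation the effect-driven rule (capped at 300 per arm) has about 75% power, against 67% for a fixed 82 per arm. The damage is an erratic N and a possible excess of false positives, rather than lower average power.

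The reply does not remove the core. The article itself announces the recalculation, words it so that the harmful and harmless rules both comply, and gives two counts for one phase.

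**Conclusion.** The concern holds in conditional form. Any reading gives an imprecise N from 20 patients: about 55 to 200 per arm with the blinded s.d., and close to noise if the observed difference is used. In the latter case, with pilot patients retained and no adjustment, type I error is about 6 to 8.5% depending on floor and cap, or about 5.4% with a floor of 82 per arm. With a blinded s.d.-only rule, or with pilot patients left out of the final test, it stays at about 5%. These figures rest on normal scores with s.d. 8 in both arms.

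The mismatch between 20 patients and 10 cases is a matter of text and needs no assumption, although a benign explanation is possible. The issue should be settled before any pilot outcome is seen; it is not a fatal flaw.

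**What to change.** - In Statistical considerations, state that any re-estimation uses only the blinded pooled s.d., with the 3-point target held fixed. Preferably do this at a later and larger count than 20.
- Do not let N fall below the planned size once that size is corrected. The stated inputs give 112 per arm, not 82. Either correct the figure or state the s.d. that supports 82.
- State that no between-arm efficacy comparison is made before the final analysis, and say whether pilot patients enter it.
- Reconcile the pilot count in Statistical considerations with the interim count in Operative complications, and say what the latter analysis covers.

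These are changes of wording. What is lost is an early effect estimate, which at ±7.5 points is uninformative. Correcting the planned size would enlarge the trial, but that cost comes from the present miscalculation and not from the re-estimation rule.

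### The superiority sample size of 164 does not follow from its printed inputs, which give 224 evaluable patients if the one stated SD of 8 applies to both arms

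*Protocol article*

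**What the plan says.** All the relevant text is in the protocol article, Statistical considerations.

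- **Superiority.** The trial is powered on the primary outcome alone. Alpha is 0.05 and the quantity printed as beta is 0.8, which can only mean power. The other inputs are "a randomization ratio of 1: 1 and a mean(s.d.) GERD-HRQL score of 8(8) after LF" and a mean of 5 after LRYGB, taken from a different source and printed without an SD. The conclusion is "a sample size of 164 would be required. Assuming a 10 per cent dropout, there would need to be 91 patients in each arm".
- **Non-inferiority.** A second calculation covers the possibility that LRYGB gives the same mean as LF. It uses alpha 0.05, 0.9 for power (again printed as beta), the same 8 (8) for LF, and "a non-inferiority limit (d) of 4, a sample size of 138 is required".
- **Testing.** P "values will be two-tailed (except for non-inferiority analysis"), and "significance will be set at 0.050". Continuous outcomes are compared with a t test or a Mann–Whitney U test. No baseline adjustment is mentioned.
- **Pilot.** The section says that data to guide the calculation are limited, and that power and trial duration will be recalculated after a 20-patient pilot.

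**The concern.** The section prints what looks like a full set of inputs together with the answer, and the two disagree by 60 patients (224 − 164), or 27% of 224. That is too large to be rounding. The superiority figure is the larger of the two calculations, so it sets the size of the trial. The recruitment estimates in the same paragraph follow from it.

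If SD 8 was meant for both arms, the trial would miss a true 3-point difference about one time in three while being described as having 80% power. A null superiority result would then be given more weight than the design supports.

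**Working it through.** **Inputs** (all from Statistical considerations): two-sided alpha 0.05, z = 1.960; power 0.80, z = 0.8416; means 8 and 5, difference 3; SD 8 for LF; no SD for LRYGB; 1:1 allocation; 10% dropout.

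**1. The plan's figure, with SD 8 in both arms.**

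n per arm = 2 × (z_alpha + z_power)² × SD² / difference² = 2 × (1.960 + 0.8416)² × 64 / 9 = 111.6, so 112 per arm and 224 in total. The plan says 164 (82 per arm).

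**2. Other readings of the same inputs.**

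- One-sided alpha 0.05: 2 × (1.645 + 0.8416)² × 64 / 9 = 87.9, so 88 per arm and 176 in total.
- Two-sided with the t distribution: 113 per arm, 226 in total.
- Mann–Whitney, at relative efficiency 0.955: about 236 in total.

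None gives 164.

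**3. Power at 164 evaluable, SD 8 in both arms.**

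SE = 8 × √(2/82) = 1.249. Power = Φ(3/1.249 − 1.960) = Φ(0.441) = 67.0% (66.5% with the noncentral t). The difference detectable with 80% power is (1.960 + 0.8416) × 1.249 = 3.50 points. If all 182 randomised patients were evaluable, power for 3 points would be about 72%.

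**4. Allowing for dropout.**

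112 / 0.9 = 124.4, so 125 per arm and 250 randomised, against the planned 2 × 91 = 182.

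**5. The non-inferiority figure, as a check.**

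With true difference 0, one-sided alpha 0.05, 90% power and SD 8 in both arms: 2 × (1.645 + 1.2816)² × 64 / 4² = 68.5, so 69 per arm and 138 in total. This reproduces exactly, and 69 / 0.9 = 76.7 gives the stated 77 per arm. It confirms that the value printed as beta is power, and that this calculation used SD 8 in both arms.

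**6. What would give 164.**

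With unequal SDs, n per arm = (8² + s²) × (1.960 + 0.8416)² / 9, where s is the LRYGB SD. At s = 5.4 this is (64 + 29.16) × 7.849 / 9 = 81.2, so 82 per arm and 164 in total. Two other unstated inputs would also do it: a common SD of about 6.86 with a 3-point difference, or a difference of about 3.5 with SD 8.

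**7. Range over the missing LRYGB SD** (an assumption, since the document gives no value; two-sided, difference 3, LF SD 8):

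| LRYGB SD | Total needed for 80% power | Power at 164 evaluable |
|---|---|---|
| 5 | 156 | 82% |
| 5.4 | 164 | 80% |
| 6 | 176 | 78% |
| 7 | 198 | 72% |
| 8 | 224 | 67% |

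**The case against.** The strongest reply is that the inputs are incomplete rather than the arithmetic wrong. The SD of 8 is attached to LF only, and the LRYGB mean comes from a separate source. An LRYGB SD near 5.4 beside a mean of 5 is not contrived, since LF has SD 8 beside a mean of 8, and it gives exactly 164 with 80% power. A journal article condenses a fuller protocol, so a second SD could have been lost on the way. The match at 138 does not settle the matter: that calculation assumes equal means, where carrying the LF SD into both arms is natural.

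This stands to the extent that a reader might infer that the trial's true power is 67%, and the document does not support that as an unconditional statement. The non-inferiority match supports a common SD of 8 but does not prove that the superiority calculation used it.

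It does not rescue the printed figure. If an SD of about 5.4 was used for superiority, the two calculations in one section rest on different variances for the same outcome, and neither the value nor the reason is given. The difference matters: SDs of 8 and 5.4 in the non-inferiority formula would give (64 + 29.16) × (1.645 + 1.2816)² / 16 = 49.9, so 50 per arm and 100 in total rather than 138.

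A second reply is that the pilot will prompt a recalculation, so 164 is provisional. That is true and softens the consequence, but it does not make 164 follow from its inputs. A recalculation that starts from an unclear SD or difference would carry the problem forward.

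**Conclusion.** The superiority sample size is wrong as written: 164 cannot be obtained from the inputs printed beside it, under two-sided or one-sided testing, and nothing elsewhere in the article supplies the missing input. This part rests on no assumption beyond the standard two-mean formula and the one SD that is given.

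The size of the shortfall is conditional. With SD 8 in both arms and a 3-point difference, 224 evaluable patients are needed rather than 164. With an LRYGB SD between 5 and 8, power at 164 runs from about 82% down to about 67%. A common SD of 8 is the more natural reading because it is the only SD stated and the one behind 138, but the document leaves the other reading open.

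**What to change.** Amend the sample size paragraph in one of two ways.

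1. If a different LRYGB SD or a different difference was used, state it with its source, show that it yields 164, and explain why the non-inferiority calculation uses SD 8 in both arms.
2. If SD 8 in both arms and a 3-point difference were intended, restate that 164 evaluable patients give about 67% power for 3 points and 80% for 3.5 points. The alternative is to change the target to 224 evaluable, about 250 randomised at 10% dropout.

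In either case, carry the corrected inputs into the planned recalculation after the pilot, and label the values 0.8 and 0.9 as power rather than beta.

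The cost is one paragraph of wording. Under the first option the stated power stands. Under the second it becomes less favourable, and no extra patients are needed if the power is restated rather than the target raised.
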